| 
Statistics
 
Summary of analysis
 | 
Primary Endpoint Analysis: Day 29
 
The study is designed and will be analysed according to group-sequential methods, specifically the triangular test. The triangular test is one way of analysing group sequential trials and uses straight line stopping boundaries. It involves analysing the data as they accumulate, with points being plotted relative to a triangular region and stopping when the upper or lower boundary of the region is crossed (Graph 1). It has the advantage over other methods of analysing group sequential trials, such as the discrete sequential probability ratio test, in that a closed continuation region is used ensuring that the trial stops within a pre-specified maximum sample size.
 
The type I error rate and power of the study were set to 5% and 95%, respectively (<math>\alpha=0.05</math>, <math>\beta=0.05</math>) with parameters <math>p_0=0.75</math> and <math>p_a=0.90</math>. Based on these specifications, the boundaries of the test were calculated for the null hypothesis, <math>H_0: p \leq p_0</math>, and the alternative hypothesis, <math>H_a: p > p_0</math> (see Graph 1). Based on the rationale above, rejecting the null hypothesis, <math>H_0: p \leq p_0</math>, (crossing the upper boundary) means that we can consider the regimen for compassionate use while failing to reject the null hypothesis (crossing the lower boundary) means that we cannot consider the regimen for compassionate use. Data from each arm will be analysed (for the evaluable patient population or per protocol analysis) after every 10 patients reach the primary endpoint of initial cure, where the actual values of Z and V will be calculated and then plotted on the graph. Depending on where the point falls, that arm of the trial will either continue collecting data for another 10 patients or will stop, concluding with a rejection of the null hypothesis (adequate efficacy) or a non-rejection of the null hypothesis (inadequate efficacy). In the final analysis, asymptotic properties will be used to calculate unbiased estimators of the response rate and its 95% confidence interval taking into account the sequential nature of the analyses.
 
Secondary Endpoint Analysis:
 
When the analyses concludes that an arm should be stopped (i.e. a boundary has been crossed), survival at 1 year will also be evaluated. Due to sequential design employed and the different treatment options to be determined by day 29 outcomes (i.e. repeat treatment and/or pentamidine prophylaxis), subsequent analyses (i.e. the secondary endpoint) are likely to be descriptive only. Such descriptive analyses will focus on survival (alive and disease-free) at 12 months post day 29 assessment and relapses between day 29 and 12 months follow-up, by arm and day 29 outcome.
 
Safety Analysis
 
Adverse events (AEs) will be described on treatment and during follow-up. AEs will be coded using MedDRA and tabulated by severity / CTC V4 AE grading. Causality of AEs will also be tabulated. Serious Adverse Events (SAEs) will be described by individual narratives based on the SAE reports provided by the site investigators. Summary statistics will be tabulated for haematological and biochemical parameters as well as for ART efficacy (CD4 count, viral load) at each time point.
 |

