### **9.1. Rules in case of treatment suspension or interruption**

In the event that treatment is interrupted (e.g. due to an adverse event), the decision to resume treatment will be taken by the site Principal Investigator.

If miltefosine treatment is interrupted for more than 3 days and requires additional VL treatment (other than that described in the protocol) they will be considered a treatment failure for the purposes of the ITT analysis and excluded from the per protocol analysis. If interruption was for 3 or less days, treatment will start again till the complete dose is administered.

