## 10. Data Analysis and Statistical Methods

### 10.1. Sample size determination

The sample size will be determined according to the sequential design for the primary outcome to be measured at day 29.

Since we are using a sequential approach, the sample size is not defined or known in advance. The maximum sample size needed per arm would be 66 patients (132 total patients) and the maximum analyses performed would be 7 (see Graph 1, upper horizontal axis). The actual sample size may be less than this, with its value depending on the value of the proportion cured.

Graph 1: Triangular region for study arms showing the boundaries for analysing the sequential trial using the Triangular Test, with the following parameters ( $p_0 = 0.75$ ,  $p_a = 0.9$ ,  $\alpha = 0.05$ ,  $\beta = 0.05$  and  $n = 10$ ).

[figure not shown]

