### 10.2. Definition of study populations included in the analysis

For the sequential and primary analysis (day 29), an intention to treat (ITT) and per protocol (PP) analysis will be performed.

To take account of missing data, each of the above analysis sets (ITT and PP), the efficacy endpoint will be calculated in two ways:

- complete case analysis: excluding patients with missing efficacy data from estimation of efficacy
- worst case analysis: patients with missing efficacy data will be allocated efficacy results based on their 'worst-case' scenario i.e. treatment failure.

Missing outcome data on the efficacy endpoints could arise if a patient withdraws consent, is lost to follow-up, or has an exam omitted by investigator oversight.

The ITT complete case analysis will be primary.

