#### **10.9. Interim analysis**

There will be sequential analysis every 20 patients (10 patients in each arm), up to completion of the study. A maximum of 7 analysis will be performed. DSMB will consider if both treatment arms should be continued based on pre-defined criteria set in the sequential analysis. DSMB will also review the available safety data (AEs, SAEs) for both treatment arms.

In order for the findings of this study to be generalizable the population included in this study is heterogeneous (i.e. includes relapse and primary VL patients, patients currently on ART and those that will start ART). In order to address potential concerns regarding the heterogeneity of the population and reduce the likelihood of rejecting a treatment that may be effective in a sub section of the population a test to assess heterogeneity will be performed when a treatment is stopped. This test will be

conducted to verify on the available data if there is a signal of interaction ( $p < 0.10$  = possible interaction) between strata (primary VL or relapse; patients currently on ART or patients initiated on ART during the study) and treatment (magnitude of the treatment effect is dependent upon strata). In absence of signal of interaction ( $p > 0.10$ ) the magnitude of the difference in success rates between treatments should be relatively homogeneous across strata. In presence of significant signal interaction, the treatment effect will have to be adjusted on strata to know whether both therapeutic strategies have the same success rate. Depending on the outcome of this test for heterogeneity, recruitment may be continued into one stratum. This decision will be taken by the sponsor following consultation with the DSMB and other relevant authorities.

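### The synopsis plots the stopping boundaries for an evaluable or per-protocol set, Section 10.2 makes ITT complete case primary, and no passage says which set decides whether an arm stops

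*Protocol*

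**What the plan says.** The synopsis (Statistics, Primary Endpoint Analysis: Day 29) sets out the decision rule. After every 10 patients in an arm reach the day-29 endpoint, Z and V are calculated and plotted against the triangular region. On the population it says: "Data from each arm will be analysed (for the evaluable patient population or per protocol analysis". On the consequence it says: "crossing the upper boundary) means that we can consider the regimen for compassionate use". Crossing the lower boundary means the regimen cannot be considered for that use.

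Section 10.2 says: "For the sequential and primary analysis (day 29), an intention to treat (ITT) and per protocol (PP) analysis will be performed". Each set is to be calculated twice, once leaving out patients with missing efficacy data (complete case) and once counting them as failures (worst case). It ends: "The ITT complete case analysis will be primary".

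Section 9.1 treats one group differently in the two sets. If miltefosine is interrupted for more than 3 days and additional VL treatment is needed, "they will be considered a treatment failure for the purposes of the ITT analysis and excluded from the per protocol analysis".

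Section 10.6 defines day-29 failure to include withdrawal (with absconding as an example) and death, and calls for both ITT and per-protocol analysis. Section 10.9 refers to the DSMB applying pre-defined criteria. Neither says which set the boundary uses.

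**The concern.** A sequential test needs one sample path. As written there are at least two: a per-protocol path (synopsis) and an ITT path (Section 10.2). A third is possible, because *evaluable* is undefined. If the paths disagree at a look, the protocol has no rule for choosing between them, and a choice made after seeing the data gives up the error control that the design is meant to provide.

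The difference between the paths is not random. The one per-protocol exclusion that the protocol spells out removes patients who are failures under ITT. Removing failures raises the observed cure rate and moves Z upwards. That exclusion depends on miltefosine, so as written it can arise only in the combination arm. At stake is the trial's main result for that arm, and with it the decision on compassionate use.

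**Working it through.** **Inputs from the protocol.** p0 = 0.75 and pa = 0.90 (Section 10.1, Graph 1 caption). "The type I error rate and power of the study were set to 5% and 95%, respectively" (synopsis). One-sided test of p ≤ p0 in each arm, with looks every 10 patients per arm. Stated maximum: "The maximum sample size needed per arm would be 66 patients (132 total patients) and the maximum analyses performed would be 7" (Section 10.1).

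**Step 1: reproduce the stated design.** Triangular test for one proportion.

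- θ = logit(0.90) − logit(0.75) = 1.0986
- Z = S − 0.75n, where S is the number cured; V = 0.75 × 0.25 × n = 0.1875n
- a = (2/θ) ln(1/(2 × 0.05)) = 4.192; slope c = θ/4 = 0.2747
- Correction for looks of 10: 0.583 × √1.875 = 0.798, so a′ = 4.192 − 0.798 = 3.394
- Upper boundary: Z = 3.394 + 0.2747V. Lower boundary: Z = −3.394 + 0.8240V
- The lines meet at V = 3.394/0.2747 = 12.36, so n = 12.36/0.1875 = 65.9

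This gives 66 per arm and 7 looks, as stated, so these are the intended boundaries.

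**Step 2: boundaries in numbers of cures.**

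| n in the set | adequate | inadequate |
|---|---|---|
| 10 | not reachable | ≤5 |
| 20 | 20 | ≤14 |
| 30 | ≥28 | ≤23 |
| 40 | ≥36 | ≤32 |
| 50 | ≥44 | ≤41 |
| 60 | ≥52 | ≤50 |
| 70 | ≥60 | ≤59 |

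The continuation region at n = 50 is only 42 to 43, and at n = 60 only 51. A few patients moved in or out can therefore change the decision.

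**Step 3: one worked example.** At a regular per-protocol look with 28 of 30 cured:

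- Z = 28 − 22.5 = 5.50; upper boundary = 3.394 + 0.2747 × 5.625 = 4.94. Result: adequate.

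Add back 5 patients excluded from per protocol but counted as ITT failures, giving 28 of 35:

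- Z = 28 − 26.25 = 1.75; lower boundary = −3.394 + 0.8240 × 6.5625 = 2.01. Result: inadequate.

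This needs 5/35 = 14% excluded, and the ITT count of 35 falls between scheduled looks. It shows that opposite readings of the same patients are possible, not that they are typical. The fewest excluded failures that produce such a reversal are 6, 5, 4, 3 and 2 at per-protocol looks of 20, 30, 40, 50 and 60.

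**Step 4: chance of declaring an arm adequate.** Assume a true ITT cure rate of 0.75 and that a share e of patients are ITT failures dropped from per protocol. The per-protocol cure rate is then 0.75/(1 − e). Exact binomial calculation, looks at 10 to 70 in the set used:

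| share excluded (assumed) | per-protocol cure rate | chance of adequate |
|---|---|---|
| 0 (ITT boundaries) | 0.750 | 4.1% |
| 1% | 0.758 | 5.2% |
| 2% | 0.765 | 6.7% |
| 3% | 0.773 | 8.6% |
| 5% | 0.789 | 13.8% |
| 8% | 0.815 | 26.8% |
| 10% | 0.833 | 39.6% |

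**Step 5: disagreement when both paths keep looks of 10.** In 20,000 simulated trials per setting with ITT cure 0.75, ITT ended inadequate and per protocol adequate in 9.5%, 22.9% and 35.4% of trials at 5%, 8% and 10% excluded. The reverse did not occur.

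**The case against.** Several points on the other side have force.

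- *Evaluable* can fairly be read as patients with a day-29 result, which is close to ITT complete case. On that reading half of the synopsis phrase agrees with Section 10.2, and only the per-protocol alternative clearly conflicts. Section 10.2 also names one primary set, so the body text can be said to rank the sets already. It does not say, however, that the ranking governs stopping, and it runs both sets sequentially.
- No per-protocol exclusion rate is given. The Section 9.1 exclusion needs both a long interruption and additional VL treatment, and Section 15.3 describes gastrointestinal symptoms severe enough to stop miltefosine as infrequent (not specifically in HIV co-infection). The true share may be small. At 1% to 3% the chance of a wrong adequate result is 5.2% to 8.6%, a modest excess.
- A reader might infer that the type I error is broken outright. That goes too far. If per protocol is the tested population, its cure rate in Step 4 exceeds 0.75 and its own null is false. The excess exists relative to the ITT null, which matters because Section 10.2 makes ITT complete case primary.
- A reader might also infer that the wording tilts a comparison between arms. The documents do not support this: Section 3.3 says a comparative study is not possible, and each arm is tested separately against 0.75. Nor can it be said that exclusions arise only in the combination arm. That is true of the one exclusion written in Section 9.1, but the full per-protocol definition may sit in the SAP, and whether deaths or withdrawals leave the set is not stated.

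None of these points says which path decides.

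**Conclusion.** The point stands as a contradiction in current text, and it is wrong as written. The synopsis and Section 10.2 name different sets for the same stopping decision, and no passage resolves it. Under the Section 9.1 exclusion the direction is known: per-protocol boundaries make adequate efficacy easier to reach in the combination arm relative to the ITT null of 0.75.

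The size depends on an unknown. Against 4.1% with ITT boundaries, the chance of an adequate result at a true ITT cure rate of 75% runs from 5.2% at 1% excluded to 39.6% at 10%. These figures assume that every excluded patient is an ITT failure; with fewer failures among those excluded, the effect is smaller. The contradiction itself does not depend on the exclusion share.

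**What to change.** In the synopsis and Sections 10.2 and 10.9, name one set for Z and V at every look and in the final test: the ITT set that Section 10.2 already makes primary. Strike the per-protocol alternative from the synopsis sentence, and either define *evaluable* or remove it. State that per-protocol results are supportive and play no part in stopping.

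State the missing-data rule for that set alongside. Section 10.2 lists withdrawal of consent and loss to follow-up as sources of missing data, which complete case leaves out, while Section 10.6 counts withdrawal, absconding and death as failures. The two must be reconciled so that each such patient has one status at each look. This is a decision on missing-data handling, not only an edit of wording, and it should be made before the first look.

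The boundaries, sample size and looks do not change. The cost is an amendment to the text, and the combination arm loses a favourable exclusion.

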## 1. Background and Study Rationale

### Background

#### Epidemiology

In 2009, 33 million people were reported to be living with HIV/AIDS with 2.6 million of which were newly infected; 69% of these new infections occurred in sub-Saharan Africa. Leishmaniasis is recognized as one of the most neglected diseases with 12 million people infected and 2 million new infections annually. Of these 500,000 are with visceral leishmaniasis. The two epidemics geographically overlap and the first cases of co-infection were reported from southern Europe in 1985. Since then, a considerable amount of knowledge and experience has been accumulated that can be summarized as follows:

HIV and VL mutually influence each other as they both affect cellular immunity; as a consequence, the risk of VL may be up to 2300 times higher in an HIV-infected individual. Conversely, concurrent VL accelerates HIV progression.

VL occurs in co-infected patients when they have already developed advanced HIV disease (AIDS); in virtually all patients CD4 count at presentation are below 200 cells/mL.

Co-infected patients have ample parasites circulating in the peripheral blood that contribute to transmission by the sandfly vector. In the Mediterranean most co-infected cases were seen in Spain among IV drug abusers; a new transmission cycle was found by means of the sharing of used needles without the need for the sandfly vector.

While the clinical presentation is not essentially different, co-infected patients may also have atypical presentations and clinical suspicion of VL may be decreased as in HIV/AIDS patients classical clinical signs and features such as splenomegaly and pancytopenia may be caused by other HIV-related pathology or medication.

While parasitological diagnosis is on average more sensitive in co-infected patients, serodiagnosis is cumbersome because of poor humoral antibody responses. This is of concern as many patients relapse and may be reluctant to undergo repeated invasive diagnostic procedures such as bone marrow aspiration.

The most important problem is treatment; when compared with VL patients who are not infected with HIV, cure rates for HIV co-infected patients are lower, drug toxicity is increased and mortality rates are higher. Relapses are common; studies have shown that most if not all are true relapses with the same leishmania strain although some new infections may also occur. Persistent low CD4 counts may play a role and with each relapse the response to treatment is lower.

The incidence of cases in the Mediterranean area has decreased with the introduction of anti-retroviral therapy (ART); it is probable that ART prevents asymptomatic patients from becoming symptomatic by restoring immunity.

While the epidemic of co-infection has decreased in the Mediterranean area, with further spread of HIV in VL endemic areas, an increase in co-infected cases has been reported in Africa (Ethiopia) and in Latin-America (Brazil).

In Ethiopia the national HIV prevalence is 2.1% (MoH, 2007). VL is reported from at

least 40 areas but 60% of cases occur in the Metema and Humera lowlands. Co-infection rates range from 18-31%. Most patients are young men who are among the 300 - 500,000 migrant workers who come each year from the highlands to work in the agricultural schemes; while some are already infected on arrival, it is assumed that others contract HIV by visiting local sex workers.

In Brazil, the number of VL cases is increasing country-wide as is the number of co-infected patients. This is thought to be related to the increasing urbanization.

### **Treatment options for visceral leishmaniasis**

Current treatment options and their limitations are summarized in Table 1.

**Table 1: Current treatment options for patients with visceral leishmaniasis**

| Drugs                    | Limitations                                                                                                                                                                                                                |
|---------------------------------|-----------------------------------------------------------------------------------------------------------------------------------------------------------------------------------------------------------------------------------|
| Pentavalent antimonials  | toxicity (pancreatitis, hepatitis and cardiotoxicity: arrhythmias)
30 day iv/im treatment in hospital
painful injections                                                                                                    |
| Amphotericin B           | Needs slow IV infusion; infusion reactions (fever);
nephrotoxic; needs lab monitoring                                                                                                                                          |
| Liposomal amphotericin B | expensive
requires slow iv infusion over 1-2 hours
however long term hospitalization is not required                                                                                                                        |
| Miltefosine              | teratogenic
expensive
GI toxicity, hepato- & renal toxicity                                                                                                                                                                 |
| Paromomycin              | an aminoglycoside, therefore nephro- and ototoxicity possible: although reversible high tone audiometric shift may occasionally occur during treatment (Sundar, et al. 2007);
geographical variation in response (Hailu, 2010) |
| Pentamidine              | IM injection
Risk of developing diabetes mellitus                                                                                                                                                                              |

In recent years, there has been increasing interest in developing combination regimens that offer the benefit of short duration therapy with reduced toxicity and cost, while maintaining or improving efficacy. In East Africa, a randomized, comparative study of SSG monotherapy (20 mg/kg for 30 days), paromomycin sulphate (PM) monotherapy (20 mg/kg for 21 days) and combination treatment

consisting of PM at 15 mg/kg/day + SSG at 20 mg/kg/day for 17 days (LEAP 0104B) has now been completed and will be reported soon.

Currently a phase II study is being conducted in non-co-infected VL patients that looks at the combination of AmBisome (single dose 10 mg/kg) + SSG 20 mg/kg for 10 days, AmBisome (single dose 10 mg/kg) + miltefosine (2.5 mg/kg for 28 days) and miltefosine monotherapy (2.5 mg/kg for 28 days) (LEAP 0208).

### **Current knowledge on treatment options for co-infected patients**

The treatment of VL patients co-infected with HIV differs considerably from immunocompetent VL patients; the currently available information is summarized below and in Table 2 (studies in the Mediterranean area) and Table 3 (studies in other areas).

1. SSG. A large RCT in Ethiopia has shown an initial efficacy for SSG in co-infected patients of about 90%. However, this figure excludes patients that died during treatment where there was a clinical suspicion that they may have been HIV positive but their HIV status was never confirmed. For the comparator arm with miltefosine, the initial cure rate was 78%. All treatment failures in both arms were treated further with SSG; this resulted in end-of-treatment cure rates of 90 and 89%, for those treated initially with SSG and miltefosine, respectively. At 6 months follow-up, relapses were found in 11% and 25%, respectively. SSG caused more severe side-effects such as severe pancreatitis and increased mortality; the risk of death was increased with a factor 6.35 (95% CI 2.5-16.9). In a retrospective study cure rate was lower SbV at 68%. Another study showed that SbV may stimulate HIV replication.
2. Paromomycin. There are no data on toxicity and safety in co-infected patients. In HIV negative patients considerable differences in efficacy exist between India and African countries, with unacceptable low cure rates in Sudan. There are concerns about resistance that is readily induced *in vitro* and may occur after prolonged administration in CL patients. Generally it is felt that in Africa PM should only be used in combination with other drugs in particular in Sudan. SSG + PM combination is the current WHO recommended treatment for VL patients in East Africa.
3. Amphotericin B (AMB). This is no longer used in Western countries as safer drugs are now available; it has been widely used in India but is now superseded by miltefosine. In co-infected patients efficacy is equal to that of SbV (initial cure rates 58-82%) with renal toxicity occurring in 18-36%.
4. Liposomal Amphotericin B (Ambisome®). AmBisome is considered safe even also in HIV co-infected patients. It was shown to be effective in Europe in doses of 30-40 mg/kg but it did not prevent relapses. In Ethiopia, cure rates with total dose of 30mg/kg are unacceptably low in HIV co-infected patients. MSF in Ethiopia records a 74% cure rate in primary VL. There is little information from other endemic areas; experience from a number of centres in

the state of São Paulo, Brazil seem to give similar low cure rates with monotherapy AmBisome® at 21 mg/kg total dose in co-infected patients. The official WHO recommendation is 40 mg/kg total dose based on (limited) experience in Europe (table 2).

5. Miltefosine. In a RCT in Ethiopia MF was safer than SSG but efficacy was lower with a relapse rate of 31% (also see above under SSG). It is potentially teratogenic implying the use of adequate contraceptive cover in women of child-bearing age. Because of the long-half life, this should be maintained for 4 months after treatment when used for 28 days.
6. Pentamidine. There is no information on its use in the primary treatment of VL in co-infected patients; it is mainly used as secondary prophylaxis. It is well-distributed in tissues and slowly excreted. While in previous treatment studies in HIV-negative patients toxicity is well described (mainly development of diabetes mellitus), no serious side-effects are noted when pentamidine is used as secondary prophylaxis.

